## Abstract

**Background:**

The United Nations Millennium Development Goals include targets for the health of children under five years old. Poor health is linked to poverty and microfinance initiatives are economic interventions that may improve health by breaking the cycle of poverty. However, there is a lack of reliable evidence to support this. In addition, microfinance schemes may have adverse effects on health, for example due to increased indebtedness. Rojiroti UK and the Centre for Promoting Sustainable Livelihood run an innovative microfinance scheme that provides microcredit via women’s self-help groups (SHGs). This pilot study, conducted in rural Bihar (India), will establish whether it is feasible to collect anthropometric and mortality data on children under five years old and to conduct a limited cluster randomized trial of the Rojiroti intervention.

**Methods/Design:**

We have designed a cluster randomized trial in which participating tolas (small communities within villages) will be randomized to either receive early (SHGs and microfinance at baseline) or late intervention (SHGs and microfinance after 18 months). Using predesigned questionnaires, demographic, and mortality data for the last year and information about participating mothers and their children will be collected and the weight, height, and mid upper arm circumference (MUAC) of children will be measured at baseline and at 18 months. The late intervention group will establish SHGs and microfinance support at this point and data collection will be repeated at 36 months.

The primary outcome measure will be the mean weight for height z-score of children under five years old in the early and late intervention tolas at 18 months. Secondary outcome measures will be the mortality rate, mean weight for age, height for age, prevalence of underweight, stunting, and wasting among children under five years of age.

**Discussion:**

Despite economic progress, marked inequalities in child health persist in India and Bihar is one of the worst affected states. There is a need to evaluate programs that may alleviate poverty and improve health. This study will help to inform the design of a definitive trial to determine if the Rojiroti scheme can improve the nutrition and survival of children under five years of age in deprived rural communities.

**Trial registration:**

Clinicaltrials.gov (study ID: NCT01845545). Registered on 24 April 2013.

## Background

The direct link between poverty and poor health was recognized in Europe in the nineteenth century [1]. More recently the World Health Organization Commission on Social Determinants of Health reported that the poor have high levels of illness and premature mortality. In all countries, at all levels of income, health and wellbeing follow a socioeconomic gradient, namely that, the lower the wealth and social class, the worse the health [2]. The United Nations Millennium Development Goals (MDGs) 1C and 4A [3] have focused the world’s attention on reducing malnutrition and mortality in children under five years of age.

Microfinance schemes provide small loans to poor families to allow them to establish income-generating activities that can potentially break the cycle of poverty. Microfinance has been shown to reduce poverty, particularly among female participants, and is recognized as a means to reduce overall village-level poverty in participating communities [4]. There is some suggestion that in addition to direct economic benefits, microfinance initiatives reduce malnutrition in children [5] and have large and positive effects on relative changes in children’s health [6]. However, there is a lack of robust evidence to support this [7] and as yet there are very few randomized control trials (RCTs) in this field of research [8].

### Need for a trial

Since its conception by Muhammud Yunus in 1978, in Bangladesh, microfinance has developed at an astounding pace. It has been credited with alleviating poverty, improving health, enhancing women’s empowerment, and bringing about a myriad other social improvements [9]. However, as early as the 1990s, the reliability of the evidence in support of microfinance was being questioned [10]. This was soon followed by the crash of the microcredit industry in Bolivia and then in several other countries, culminating in a major crisis in 2010 in Andhra Pradesh, India, where suicides among rural borrowers who faced overwhelming debts were coupled with vicious collection tactics from institutional lenders [11]. Since then there has been an increasing demand for an evidence based approach to evaluating such programs. A systematic review of the impact of microfinance on the wellbeing of poor people concluded that it could neither support nor deny the notion that microfinance is pro-poor and pro-women [8]. There is an urgent need for rigorous evaluation of microfinance programs to ensure that such initiatives indeed bring the social and health benefits that they promise and, more importantly, do not harm the communities they claim to support [12]. Randomized experiments provide a powerful method for evaluating the impact of providing microfinance to previously unserved communities [6]. Provision of microfinance is, however, a complex intervention with several social and economic interacting components. Whilst randomization may reduce bias and confounding, a careful assessment using both qualitative and quantitative methods would be required to fully evaluate the true impact of microfinance [13].

While there is a great need to resolve whether microfinance initiatives bring any health benefits to the participating communities, it is recognized that there are several potential impediments to implementing a RCT protocol and the acceptance of this approach in this setting [8]. Here we describe a pilot study to examine the feasibility of conducting a cluster randomized trial in this rural Indian community, and to make an initial assessment of the Rojiroti microfinance scheme on the nutrition and survival of children under five years of age. The results will inform the design of a larger, definitive trial of the health effects of the Rojiroti scheme.

### The Rojiroti model of microfinance

The reason cited for the disastrous consequences of conventional microfinance initiatives, such as was seen in Andhra Pradesh, is the adoption of these programs by large commercial institutions primarily motivated by profit [14]. It has therefore been suggested that microfinance providers need to return ownership to the borrowers [14]. The United Kingdom Department for International Development (DFID) supports the Rojiroti program which uses an innovative approach for providing microfinance [15]. The program is run in areas of eastern Uttar Pradesh and parts of Bihar in India by the Centre for Promoting Sustainable Livelihood (CPSL) [16]. CPSL staff enter villages and identify volunteers from the village community itself who go on to establish self-help groups (SGHs). The members of the SHG are encouraged to save money in a common pool to subsequently become eligible for a loan from the SHG itself and from CPSL. The loans are made for any purpose agreed upon within the SHG and are not restricted to conventional income-generating activities, as in conventional microfinance programs. Experience of workers in the field suggests loans are initially used for transport to government-subsidized shops and for hospital visits. As SHGs mature, later loans might be used to purchase livestock and improve housing. The approach offers a process of supporting community development at a low cost and aims to empower local villagers in managing their own finances.

### Objective

The initial objective is to determine if it is feasible and acceptable to obtain informed consent and randomize villages in Bihar to intervention or control arms of a trial, to weigh and measure children and collect mortality data. If feasible, we will also collect sufficient pilot data regarding the effects of the intervention to allow us to subsequently establish an adequately powered definitive cluster randomized trial to evaluate the effect of the Rojiroti model of microfinance on nutrition and survival of children under five years of age.

### Hypothesis

Our hypotheses are that it is feasible to conduct a cluster randomized controlled trial of the Rojiroti microfinance intervention in rural India. We also hypothesize that the introduction of Rojiroti microfinance, through establishing SHGs, will improve indicators of children’s nutrition, measured on a continuous scale, such as weight for height z-score (WHZ), weight for age z-score (WAZ), height for age z-score (HAZ), and mean mid upper arm circumference (MUAC) and that the Rojiroti microfinance intervention will decrease the prevalence of underweight, stunting, wasting, and acute moderate and severe malnutrition (as measured by MUAC) and mortality among children under five years of age.

## Methods/Design

### Study setting

The research study is being conducted in four administrative blocks within the Patna district in Bihar: Dulhin Bazar, Naubatpur, Masaurhi, and Bikram (Figure 1). In 2011, Bihar had a population of 103,804,637, of which nearly 90% (92,075,028 people) lived in rural areas. Further demographic data about Bihar are presented in Table 1
[17]. The national poverty line used in India is based on minimum essential expenditure and is much lower than the World Bank figure – about $0.43/day [18]. Rojiroti targets women who are poor by Indian standards and hence, virtually all women who form Rojiroti SHGs will be well below the World Bank extreme poverty line. We have used the term 'very poor' to describe this group.

**Figure 1 Fig1:**
[figure not shown]
**Study site.** The study is being conducted in the Patna district in Bihar, India.

**Table 1 Tab1:** **Demographic and health statistics on Bihar**

	India	Bihar
**Area**	3,287,263 km^2^	94,163 km^2^
**Total population (2011 census)**	1,210,193,422	103,804,637
**0-6-year-olds (2011 census)**	158,789,287	18,582,229
**Birth rate (per 1000 population in 2009)**	22.5	28.5
**Death rate (per 1000 population in 2009)**	7.3	7.0
**Infant mortality rate (per 1000 live births in 2009)**	50	52
**Sex ratio (females:males)**	940:1000	916:1000
**Literacy rate (percentage of population)**	69	62

Statistics obtained from the Statistical Year Book 2012, India [17].

### Study design

The study is a cluster RCT. The unit of randomization is the tola; a small community within a village, comprised of around 100 people. Participating tolas are all in the same agro-economic zone. Past experience of CPSL workers shows that when SHGs are set up in one tola, news spreads by word of mouth to the neighboring villages, and other SHGs are formed in the surrounding villages; to avoid such ‘viral’ spread of SHGs, the tolas in intervention arm will be at least 15 km apart from the tolas in the control arm. The process for requesting informed consent is described below. After informed consent is obtained, and prior to baseline data collection, tolas in each pair will be randomly assigned to early or late intervention.

Feasibility will be assessed in two stages. Initially, ten pairs of tolas have been selected and randomized. Baseline data will be collected from these tolas and at this point we will review the acceptability of the data collection procedures and tools and the quality of the data collected. If the feasibility of the study is established, a further 10 pairs of tolas will be similarly randomized to evaluate the effects of the intervention on nutrition status and mortality in children under five years of age.

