### Randomization and blinding

The 10 pairs of tolas for the feasibility phase were selected by the CPSL staff and tola names converted into code numbers which were provided to the research team based at the University of Nottingham. The code numbers were randomly assigned to either early or late intervention by the researchers in Nottingham who were blind to intervention allocation. This information was transferred back to the research team in Patna and the CPSL staff who matched the randomly assigned allocations to the tola name prior to baseline data collection. The researchers in Nottingham who will perform data analysis will remain blind to the tola allocation; however it is not possible to blind the CPSL staff and participants as the formation of SHGs and provision of microfinance cannot be masked. A further 10 pairs of tolas will be similarly randomized to complete the pilot phase of the trial.

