### ‘Viral’ spread of self-help groups

Previous experience of CPSL in the region indicates that once SHGs begin in some tolas, information spreads by word of mouth through relatives and women in nearby tolas often set up their own SHGs (‘viral’ spread). In this trial, paired early and late intervention tolas will be at least 15 km apart in order to minimize viral SHGs being set up in the late intervention tolas. To monitor viral spread in this study, a local survey by CPSL staff will determine how often nearby tolas set up SHGs. The socioeconomic characteristics of group members in SHGs which formed virally will be compared with those of women in groups formed by CPSL. Where possible, consent for the collection of health outcome data will be taken and these data will be collected in the viral tolas similar to the data collection in the randomized tolas. CPSL staff will also record whether tolas assigned to the late intervention arm proceed regardless and set up their own SHGs during the first 18 months of the study.

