### Ethical issues and the consent process

Ethics committee approval has been granted by the University of Nottingham’s Medical School Research Ethics Committee (ethics reference number: J18102012) and by the Patna Medical College Ethics Committee (document dated 15 August 2013). Appropriate approval has also been obtained from the Department of Health, Government of Bihar, India (file number: −SHSB/NRC/2008/01/Part III/2615).

Informed consent will be obtained by a novel approach, approved by both ethics committees. We expect high levels of illiteracy among the potential participants and thus documented verbal consent may be more appropriate in this setting. The CPSL fieldworker will give a verbal explanation from an agreed script to the members of the SHG. This script has been translated into Hindi and will be explained by researchers who can speak both Hindi and Magadhi; a video of the process is available at the REACH project website [25]. In addition, information sheets are provided, translated appropriately. The project will be set up only if sufficient women (10 or more) express an interest in participating in the SHG. CPSL staff will discuss the study, explain the reasons for conducting such a study, what it would involve, and offer the option of participation. One resident of each tola will be asked to further consult with all the potential participants and give written informed consent on behalf of all the residents. Where there is no informed consent, the SHG will not have health data collected and will not be randomized to enter the study. The members of the SHGs will be requested to give verbal consent on a collective basis, using a show of hands to indicate willingness to participate. The consultation and collective consent will be video recorded. Individual parental consent for participating children will also be implied by the women volunteering to bring the children to be weighed and measured. If the women do not wish to participate in the study they will be given the option to form the SHGs and receive microfinance support outside of the trial.

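### The protocol states the 15 km separation once between arms and once only within pairs; the described allocation is very unlikely to deliver the arm-level version

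*Protocol article*

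**What the plan says.** The Study design section gives an arm-level rule: "the tolas in intervention arm will be at least 15 km apart from the tolas in the control arm". The section on viral spread of self-help groups gives the rule for pairs: "paired early and late intervention tolas will be at least 15 km apart", with the aim of keeping viral groups in late tolas to a minimum.

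On allocation, Study design says that "tolas in each pair will be randomly assigned to early or late intervention". Randomization and blinding adds that "The code numbers were randomly assigned to either early or late intervention by the researchers in Nottingham". The first 10 pairs are already randomised, and a further 10 are to be handled in the same way. All tolas lie in "four administrative blocks within the Patna district in Bihar" (Study setting).

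The protocol expects spread. Both Study design and the viral-spread section report that, in the implementing organisation's experience, SHGs started in one tola lead to others nearby. The viral-spread section plans a survey of nearby tolas, outcome collection in viral tolas where possible, and a record of late tolas that start SHGs in the first 18 months. Under Type of analysis, such tolas stay in their randomised arm. Women who do not wish to take part are told that "they will be given the option to form the SHGs and receive microfinance support outside of the trial" (Ethical issues and the consent process).

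**The concern.** The two rules are not equivalent. An arm-level rule limits the distance between every early and every late tola. A pair-level rule limits only the distance between the two members of a pair and leaves an early tola of one pair free to neighbour a late tola of another. The allocation was made on code numbers, and nothing in the text links it to geography across pairs.

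The distance rule is the only preventive measure against spread that the protocol states; the other measures record spread once it has happened. If late tolas form SHGs early and the intervention works, the 18-month difference in weight-for-height z-score shrinks under intention-to-treat. The pilot exists to inform the sample size of a definitive trial (Objective; Sample size and power calculations), so a diluted difference would be carried forward. SHGs formed outside the trial by women who decline are mentioned in neither distance rule.

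**Working it through.** The plan gives no derivation to reproduce: 15 km is a design rule, and no power, effect size or spread distance is stated. The check asks whether the described procedure delivers the arm-level rule.

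**Inputs from the protocol.** 10 pairs, then 20 pairs in total; 15 km; assignment within each pair; four blocks of one district; area of Bihar 94,163 km² (Table 1); at least 23 districts in Bihar (Discussion). **Assumptions.** Pairs are assigned independently by a fair draw (implied, not stated). The study area is a square of 400 to 4,094 km². The upper end is 94,163 / 23 = 4,094 km², an upper bound on the mean Bihar district. It is not the area of this district or of the four blocks.

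**Step 1: combinations covered.** With n pairs there are n × n early-late combinations, and a pair-level rule covers n of them.
- 10 pairs: 10 of 100 covered, 90 not.
- 20 pairs: 20 of 400 covered, 380 not (380/400 = 95%).

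**Step 2: an orderly layout.** Suppose every pair had one tola in each of two compact zones, with tolas of the same zone less than 15 km apart. The arms stay separated only if all pairs fall the same way, with probability 2/2ⁿ: 2/1,024 = 0.002 for 10 pairs, and 2/1,048,576 = 0.000002 for 20.

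**Step 3: area needed for a guarantee.** Two tolas of different pairs fall in opposite arms with probability 1/2. To hold under every allocation, the arm-level rule therefore needs all tolas mutually at least 15 km apart. Oler's packing bound for a square of side s is N ≤ 2s²/(√3 × 15²) + 4s/(2 × 15) + 1.
- N = 20: s = 49.2 km, about 2,420 km².
- N = 40: s = 75.1 km, about 5,650 km² (29.0 + 10.0 + 1 = 40).

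The second figure exceeds 4,094 km², and the study uses only four blocks of one district. This is a plausibility check, not a proof.

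**Step 4: simulation.** 2,000 layouts per setting, pairs placed uniformly, members at least 15 km apart, a fair draw in each pair.

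| Area (km²) | 10 pairs: late tolas with an early tola < 15 km | 20 pairs: same | 20 pairs: < 5 km | 20 pairs: median distance to nearest early tola |
|---|---|---|---|---|
| 400 | 99.9% | 100% | 94.6% | 2.1 km |
| 800 | 98.8% | 100% | 79.6% | 3.2 km |
| 1,600 | 93.8% | 99.4% | 56.1% | 4.6 km |
| 3,200 | 79.9% | 95.5% | 35.0% | 6.5 km |
| 4,094 | 72.0% | 92.4% | 28.6% | 7.4 km |

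No layout in any setting kept all early-late distances at 15 km or more.

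**Step 5: can restricted allocation repair it?** Fix the first 10 pairs by chance and take the best of the 2¹⁰ = 1,024 allocations of the other 10. At 625, 900, 1,600 and 3,600 km², the share of late tolas with an early tola within 15 km goes from about 100, 100, 100 and 94% to about 100, 98, 92 and 77%. The distance between the arms' centres grows by roughly 65% to 72% (at 1,600 km², from 5.1 to 8.8 km).

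**Step 6: dilution.** If a fraction p of late tolas received a fraction f of the intervention's effect early, the contrast would shrink by the factor 1 − p × f. The documents give neither p nor f.

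**The case against.** The pair-level sentence follows from the arm-level one, so it may be a shorter restatement of the same rule. That is fair: a reader might infer that the pair-level rule is the one in use, but the text does not settle this. It does not remove the problem. If the arm-level rule is in force, the allocation procedure lacks the constraint needed to achieve it; if the pair-level rule is, Study design overstates the safeguard.

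The simulation assumes an area and random placement, whereas field staff chose the tolas and their locations are not given. This stands, and the percentages hold only under those assumptions. The counts in Step 1 do not depend on them.

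A reader might also infer that the controls will be contaminated. The documents do not support this. The 15 km is a planned buffer, not a measured reach; spread is described only as reaching neighbouring or nearby communities, without a rate or distance. An early tola within 15 km is exposure to a risk. For the same reason no percentage loss of effect or rise in sample size can be given. A self-started SHG also need not equal the full programme, since external credit comes only after three to six months of running.

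Nor is it right that no protection exists. Separation within pairs is stated, its aim is to minimise spread and not to abolish it, and early SHG formation in late tolas will be recorded. Measuring such spread is a proper task for a pilot. The protocol already does part of what is needed; what it lacks is a single, true statement of the separation.

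**Conclusion.** The concern holds as an internal conflict with a practical consequence. Study design promises separation between arms, the viral-spread section promises it within pairs, and the described allocation does not secure the former. The pair-level rule leaves 380 of 400 early-late combinations uncovered. For 40 tolas in four blocks of one district, arm-level separation is very unlikely: 92% to 100% of late tolas would have an early tola within 15 km over assumed areas of 400 to 4,094 km², given random placement and independent assignment of pairs.

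Late tolas are therefore exposed to spread that the protocol itself expects, and any resulting dilution would pass through the intention-to-treat result into the planning of the definitive trial. Its size cannot be derived from the documents. How many SHGs form outside the trial, and where, is likewise not stated.

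**What to change.** 1. Reconcile the two statements. If the rule is pair-level, withdraw the arm-level claim from Study design. If it is arm-level, describe the constraint that achieves it.
2. Record each tola's location and report the minimum early-late distance across all tolas, not only within pairs.
3. Before the remaining 10 pairs are randomised, check candidate tolas' distances to the 20 already allocated, and prefer well-separated candidates where available.
4. Keep intention-to-treat as primary. Prespecify a secondary analysis by each late tola's distance to the nearest SHG of any origin: early, viral or outside the trial.
5. Restricting the allocation of the remaining pairs is optional. Step 5 shows that it only partly restores separation and makes arm more dependent on geography, so any restriction should be reported and acknowledged in the analysis.

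The cost is a set of location readings, one additional analysis with low precision (about 20 late tolas), and a less favourable statement of the separation. Step 3 is possible only until the second 10 pairs are randomised; Trial status reports that recruitment for them is ongoing.

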### The intervention

CPSL staff will identify village volunteers who will steer the formation of women’s SHGs in the tolas randomized to the early intervention group. Using the Rojiroti model of microfinance [15], members of the SHG will each be asked to save a small amount (Rs. 2.50 (£0.025)) every month. When required, SHG members will be able to benefit from loans from two sources: initially from their own pooled savings and, after three to six months of running the SHG, also from CPSL. Applications for loans will be made to the SHG, and the group can apply to CPSL for the funds if it cannot provide the member with the required amount. The loans can be taken for any purpose approved by the group members. The annual interest rate on a reducing balance is 18% for all loans, providing interest payments are made and at least Rs 1 (£0.01) of the principal loan (the capital borrowed) is repaid. If Rs 1 of the borrowed amount and the monthly interest are not paid, an interest rate of 24% is charged per annum. The participant seeking the loan has to specify the loan tenure when receiving the loan; in the past CPSL have recovered between 80 and 90% of the loans within this specified time [15] and ultimately 99.3% of loans are repaid. For this study, the total duration of external credit will be recorded to analyze whether this affects health outcomes.

The tolas randomized to the control arm will not receive any intervention in the initial 18 months of the study. After 18 months, CPSL staff will enter the control tolas and provide support to establish SHGs and provide microfinance in a manner similar to the process in the tolas randomized to the intervention arm.

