**Table 2 Tab2:** **Data collected at baseline survey**

**Tola level information** (Collected from village volunteer)	How many houses are there in this tola?
	How many people live in this tola?
	How many children under 5 years of age live in this tola?
	How many children were born in the last 1 year?
	How many people have died in the last 1 year?
	How many children under 5 years of age have died in the last 1 year?
**Information about mothers** (Collected from mother)	How old are you?
	Can you read and write?
	Have you ever been to school?
	How many under children under 5 years old do you have?
	Do you or your family own any land?
	Have you or your family had to sell any assets due to emergencies such as money required for medical treatment in the last 1 year?
	Can you travel outside the village without permission from your family?
**Information about children** (Collected from mother)	Age
	Gender
	Has the child received any immunization?
	Does the child have a Road to Health card?
	Was the child born at home?

The age, weight, height, and MUAC of each child under five years of age will be recorded for all children in the tola, irrespective of whether their mothers are in the SHG. The measurement will be performed by CPSL field workers. Two workers will work together to weigh and measure each child and record the measurement that both agree on. Standing height in children aged two years and older will be measured with Seca 213 Portable Stadiometer (Seca, Birmingham, UK) to the closest 1 mm. The length of younger children will be measured using Seca 210 Measuring Mat (Seca, Birmingham, UK). Weight will be measured with Libra Fitness Standing Scale (Edryl, Goa, India); younger children will be weighed in hanging scales (Venus CHS, Ace, Rajasthan, India) and smaller infants and newborns on Docbel (Braun) Baby Scales (Popular, Docbel Industries, New Delhi, India). All weights will be recorded to the closest 100 g. MUAC will be measured and recorded to the closest 1 mm using MUAC tapes provided by the UNICEF Supply Division. CPSL staff will determine and record the number of children under five years of age who have not been measured (such as children who are temporarily absent from the village and those who are ill). This will be determined by asking the village volunteers and the mothers if they know of any children who are absent.

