#### Statistical tests

Using linear regression for continuous outcomes and logistic regression for binary outcomes, we will compare measurements from children in the early intervention tolas and children in the late intervention tolas at 18 months. We will use a multilevel model to account for the clustering of children within families within tolas, and include baseline measurements of the outcome and other confounders as model covariates. Tolas are being recruited in pairs within agro-economic zones. All tolas recruited thus far are in the same zone and all tolas in the feasibility and pilot study will be in this same zone. Given that tolas have not been matched on any other characteristics, we will not account for the pairing of tolas in our analysis.

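### Allocation reaches CPSL before baseline, and unblinded CPSL field workers then measure the children, so baseline values and who is measured can depend on arm

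*Protocol article*

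**What the plan says.** The protocol article fixes the order of steps in Study design: "After informed consent is obtained, and prior to baseline data collection, tolas in each pair will be randomly assigned to early or late intervention". Randomization and blinding adds that the result went back to the Patna team and to "the CPSL staff who matched the randomly assigned allocations to the tola name prior to baseline data collection". It also says that "it is not possible to blind the CPSL staff and participants", and that the second 10 pairs will be randomized in the same way.

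CPSL has two roles. The intervention section says "CPSL staff will identify village volunteers who will steer the formation of" the women's groups in early tolas. For the weights, heights and arm circumferences, the Data collection text after Table 2 says: "The measurement will be performed by CPSL field workers".

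Entry of the individual child is described in Ethical issues and the consent process: "Individual parental consent for participating children will also be implied by the women volunteering to bring the children to be weighed and measured". The collective consent of the tola comes before randomization, but bringing a child to be measured comes after it.

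Statistical tests then says that the multilevel model will "include baseline measurements of the outcome and other confounders as model covariates".

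**The concern.** The reason given for the lack of blinding is that group formation and lending cannot be masked. That applies once the intervention starts. It does not apply at baseline: until the code is released there is no allocation to know, so a baseline free of any influence of arm was available. The chosen order gives this up, and three routes to bias open.

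- **Measurement.** Workers from the organization that delivers the scheme, with the allocation already in its hands, decide the recorded height, weight and arm circumference.
- **Ascertainment.** Which children are brought, and which absent children are named, is settled after allocation. CPSL staff count the unmeasured children by asking volunteers and mothers.
- **Mortality reports.** Baseline deaths come from a village volunteer. In early tolas CPSL picks volunteers to lead the groups, so the informant's position may differ by arm.

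At stake are the comparability of the measured cohorts and the primary estimate, because the baseline outcome is a model covariate. The order may also be carried into the definitive trial that this pilot is meant to inform.

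**Working it through.** The plan gives no figure to reproduce: it states no effect size, SD, intracluster correlation or computed sample size for the pilot. The check is one of sequence, followed by an illustration of size.

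**Sequence**

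1. Collective consent of the tola (Study design; Ethical issues).
2. Randomization of the pair (Study design).
3. Allocation matched to tola names in Patna by CPSL staff (Randomization and blinding).
4. Baseline measurement by CPSL field workers; children enter by attendance (Data collection; Ethical issues).
5. Baseline outcome used as a covariate (Statistical tests).

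Step 4 follows step 3, so what is recorded in step 4 is not protected by randomization.

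**Size, measurement route**

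Let D18 and D0 be the early-minus-late differences in mean WHZ at 18 months and at baseline, and b the baseline coefficient. Then:

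adjusted effect = D18 − b × D0.

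If D0 contains a spurious part d, the adjusted effect moves by −b × d. Neither b nor d is in the documents; the ranges are assumptions.

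- d = 0: no shift.
- b = 0.3, d = 0.05 in size: 0.3 × 0.05 = 0.015 z.
- b = 0.7, d = 0.20 in size: 0.7 × 0.20 = 0.14 z.

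If baseline is recorded too low in early tolas, the shift favours the intervention; if too high, it works against it.

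**Scale**

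- Children per tola: Table 1 gives 18,582,229 / 103,804,637 = 17.9% aged 0–6 in Bihar. Taking 5/7 of these (even ages assumed) in a tola of about 100 people gives m = 12.8.
- With 20 tolas per arm, assumed ICC 0.05 and SD 1.0: SE = √[2 × (1 + 11.8 × 0.05) / (20 × 12.8)] = √(3.18 / 256) = 0.111.
- The 95% half-width on 38 df is 2.024 × 0.1115 = 0.226 z. With SD 1.2 it is 0.271 z.

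This ignores any precision gained from baseline adjustment. A shift of 0.015 to 0.14 z is then between 0.015 / 0.271 = 6% and 0.14 / 0.226 = 62% of the half-width. More tolas would narrow the interval but not reduce the shift.

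**The two routes act in opposite ways**

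If different children attend by arm, a baseline difference s is real and persists to 18 months as roughly b × s.

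| Source of baseline difference | Effect without adjustment | Effect with adjustment |
|---|---|---|
| Spurious recording, d | not shifted | shifted by −b × d |
| Differential attendance, s | shifted by about +b × s | largely corrected, so far as baseline WHZ captures the selection |

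Neither analysis alone handles both.

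**The case against.** The strongest reply is that this is a feasibility pilot with several safeguards. Tola consent precedes randomization, so recruitment of clusters is protected. All under-fives are targeted, whether or not the mother joins a group. Two workers must agree on each measurement. Unmeasured children are counted, entries are range-checked and the analysts are blind. Nothing shows that staff would misrecord scale or stadiometer readings by arm, and the size above is assumption throughout. Data quality is reviewed after the first 10 pairs, and the effect results are only preliminary.

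Most of this stands, and it lowers the weight of the point. It does not remove it, because no safeguard blinds the baseline. Two workers in agreement are two unblinded workers; range checks find entry errors, not a shift by arm; measuring all children depends on attendance; and blinded analysts cannot undo a bias already in the data.

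Four stronger readings are not supported:

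- A reader might infer that mothers in late tolas know before baseline that they must wait 18 months. The protocol says that participants cannot be blinded, not when they learn their arm.
- A reader might infer that the people who matched the codes also measured the children. The text places both tasks within CPSL and does not identify individuals.
- A reader might infer that baseline adjustment carries every arm-related baseline difference into the estimate. This is true of spurious recording; for differential attendance, adjustment mostly helps.
- A reader might infer that bias has occurred. The document shows the opportunity only.

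**Conclusion.** The point holds as an avoidable risk of bias. The order of steps, the release of allocation to CPSL, the measurement by CPSL field workers and the entry of children by attendance are all stated outright. For recorded WHZ, the consequence is a shift of −b × d in the adjusted 18-month effect: zero if arm has no influence on recording, and about 0.015 to 0.14 z under the assumed b of 0.3 to 0.7 and d of 0.05 to 0.20. The protocol does not say whether adjustment is at child or tola level, and b depends on that. Selective attendance and arm-dependent death reports are separate and cannot be sized from the document.

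This should be fixed, but it does not invalidate the trial: the main aim is feasibility, and the first 10 baselines are already complete (Trial status). The case for acting now is that later pairs are due to follow the same procedure.

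**What to change.** **Pairs not yet randomized.** Reverse the order within each pair. In both tolas, complete collective consent, a list of all under-fives, the baseline measurements and the mortality questionnaire. Lodge these data with Nottingham. Only then release that pair's allocation to Patna and CPSL.

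**First 10 pairs.** Report by arm the numbers of children listed, measured and unmeasured, and the baseline characteristics. The unmeasured counts are already being collected. Show the 18-month effect with and without baseline adjustment and interpret the two together.

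**Cost.** Group set-up is delayed by the time needed to measure about 13 children in each of two tolas. No extra participants are needed. The second stage will have a different baseline order from the first, which should be stated in the report.

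**Limit.** The change does nothing about unblinded measurement at 18 months. The paragraph on that visit does not name the measurers; if they are again CPSL field workers, that risk remains.
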